## Abstract

**Background:**

Mobile health (mHealth) interventions that leverage social support (SS) can improve partner involvement and pregnancy experiences and promote antenatal care (ANC) attendance and skilled births. In our previous studies, we used behavioral frameworks to develop a user-centered mHealth-based, audio SMS text messaging app to support pregnant individuals to use maternity care services in rural Uganda (Support-Moms app). In our pilot study, we observed high intervention uptake, acceptability, and feasibility, as well as increased ANC attendance and skilled births.

**Objective:**

With the promising pilot data, we propose a type 1 hybrid implementation-effectiveness trial to test if this novel patient-centered automated and customized mHealth-based SS intervention is effective and cost-effective enough to warrant future large-scale implementation into Uganda’s routine maternity care.

**Methods:**

We will physically recruit 824 pregnant women at <20 weeks of gestation living in Mbarara and Mitooma districts, southwestern Uganda, and randomize them (1:1) to receive standard of care or the Support-Moms app, with at least 2 of their identified social supporters. Our primary outcome will be the proportion of skilled births. Secondary outcomes will include number of ANC visits, institution-based delivery, mode of infant delivery, preterm birth, birth weight, SS, obstetric complications, and deaths (maternal, fetal, and newborn). We will assess other implementation, service, and client outcomes through study records, the mHealth platform, and questionnaires with all women in the intervention, their social supporters, health care providers (HCPs), and managers from participating facilities. We will conduct face-to-face in-depth exit interviews with 30 purposively selected intervention participants and 15 facility HCPs and managers to explore implementation strategies for scale-up. Annual maternity resource allocations, costs, number of ANC visits, and deliveries will be assessed from facility records up to 36 months after implementation. We will estimate incremental cost-effectiveness ratios concerning cost per additional HCP-led delivery, per death averted, and per quality-adjusted life year gained as cost-effectiveness measures.

**Results:**

This study was funded in September 2023. Ethics approval was obtained in February 2024, and actual data collection started in March 2024. As of January 2025, 75% (618/824) of all projected study participants provided consent and were recruited into the study. Participants are expected to be followed up until delivery, and 15% (124/824) have so far exited. Data analysis for the trial is expected to start as soon as the last participant exits from the study. The qualitative interviews will start in April 2025, and data will be analyzed and published as soon as data collection is done, which is expected in March 2027.

**Conclusions:**

We are testing the feasibility, acceptability, and cost-effectiveness of implementing Support-Moms into routine maternity care from individual and facility perspectives. We hypothesize that Support-Moms will be an effective and cost-effective strategy to improve maternity service use for women in rural Uganda and similar settings.

**Trial Registration:**

ClinicalTrials.gov NCT05940831; https://clinicaltrials.gov/study/NCT05940831

**International Registered Report Identifier (IRRID):**

DERR1-10.2196/67049

## Introduction

### Background

While maternal mortality has fallen over the last 20 years, an estimated 300,000 women die each year from preventable causes related to pregnancy and childbirth, and 99% of the deaths occur in low- and middle-income countries (LMICs) [1]. Over 99% of infant deaths also occur in LMICs [2,3]. Persistently high maternal mortality ratios (MMRs) in LMICs are partly attributed to challenges accessing care, with undiagnosed or poorly managed pregnancy-related complications from direct or indirect causes [1]. Recurrence risks of fatal episodes increase exponentially among women who survive previous fatal episodes unless preventive measures for early detection and monitoring throughout the perinatal period are adopted [2,4-6]. Antenatal care (ANC) prevents perinatal and maternal morbidity and mortality by early detection and treatment of prenatal complications and identifying women at high risk to ensure delivery in skilled settings [7-11]. ANC supports women, their families, and communities to navigate challenges at a critical time during pregnancy; debunks misconceptions; increases information transfer; and can motivate women to seek facility delivery and care [9]. The World Health Organization (WHO) and other authorities have called for urgent evaluation of adaptable and context-specific health solutions to promote ANC uptake and maternity services to reduce maternal and early childhood mortality and morbidity [9,11-14]. Identifying and scaling up interventions that improve access to and the use of available health care in pregnancy and childbirth has the potential to prevent 823,000 stillbirths, 1,145,000 neonatal deaths, and 166,000 maternal deaths annually in the 75 highest-burden countries [2,4-6].

Despite expanded capacity to increase the number of skilled birth attendants at community facilities, Ugandan women still have low rates of ANC use and skilled births, resulting in one of the highest MMR (189/100,000) and perinatal mortality rates (34 deaths/1000 births) in the world [15]. Women’s lack of information, social support (SS), financial independence for emotional and economic provisions, decision-making autonomy regarding childbirth, birth preparedness, and perceived need for maternity care services are important challenges to using available maternity services in these settings [1,16-19]. One analysis showed that women at risk of unskilled home births needed relevant and context-specific strategies to encourage ANC attendance and skilled delivery [20]. The high cost of MMR highlights the need for adaptable interventions that boost ANC and maternity services use to reduce MMR and early childhood deaths [12].

SS is an important pillar of health promotion that has been directly linked to health care–seeking behavior, infant care practices among mothers, and HIV care in sub-Saharan Africa (SSA) [21-25]. SS can mitigate structural and physical barriers to health care access at individual and societal levels, including facilitating self-efficacy to complete positive health behaviors [26-28]. Spouses, relatives, and friends have been the sources of SS among individuals living with HIV in SSA [23-25]. Community health workers (CHWs) can provide or promote additional SS during pregnancy, leading to better health outcomes [29,30]. Village health teams (VHTs), which comprise community members identified by their community who are trained on major health programs, improve timely care seeking for facility delivery [31-35]. VHTs have historically focused on the treatment of infectious diseases, such as malaria, pneumonia, and tuberculosis [35]. Their role as an additional resource for peripartum women has not been harnessed. Therefore, social network involvement not only addresses individual but also family- and societal- or community-level barriers to care in a setting with modest availability of health centers (HCs) providing needed services [17,25,36-38].

Mobile health (mHealth) interventions can be practical, effective, and scalable tools to improve maternal health care delivery and outcomes. Many SMS text messaging and other mHealth interventions can help individuals internalize risks and potential impact of various medical conditions as well as the needs and benefits of health services [11,13]. mHealth approaches can empower individuals to seek help, address specific health concerns, strengthen informed decision-making, and improve outcomes in the perinatal period [14,39]. Scheduled SMS reminders and telephone voice messaging approaches can enable people to increase control over their health by improving knowledge transfer, learning, and comprehension. These gains may improve the perceived need to use available services, especially when interventions are well directed and executed to provide accurate and relevant information on the promoted behavior [11,13,14,25,39-42]. Several studies have found that mobile phone–based messages can be motivational as a source of individual or family SS [43], cues to action [44], or to challenge societal negative beliefs [45]. Mobile phone interventions have also been shown to increase ANC attendance [46,47], institutional delivery [48,49] and vaccination rates (such as tetanus toxoid) [11,49].

mHealth interventions that specifically bolster SS can improve pregnancy experiences by decreasing anxiety and depression [50-53] and increasing perinatal bonding [52] and communication within social networks [53]. These benefits are mediated by promoting existing family structure and social networks, which in turn foster financial and emotional coping mechanisms to enable women to overcome socioeconomic and physical barriers to care, such as food insecurity, transportation, and provision of delegated service to overcome competing priorities [25,53-55]. Community and social network engagements toward mobilization of resources to enable health care access are practical, scalable, and sustainable approaches toward participatory health care financing and use [56]**.** Although SMS alone is a convenient and lower cost approach to support health care interventions with higher delivery success, the provision of multiple messaging options, such as voice messages and social networks involvement, has been crucial to extend reach beyond the individual literate personal phone owners in SSA [57,58].

Health awareness and motivating health care use are key elements of developing effective behavior change interventions [59]. However, mHealth interventions are not always effective in improving health care and use. Whereas the failure of impact has been attributed to a mismatch between the function, adaptability, and need for mHealth interventions in some settings [11,14], end-user designs that use iterative approaches in app development can improve health care service use [60]. In a formative study, we observed that knowledge gaps influenced women’s past and future decisions to not attend ANC and pursue unskilled home births [17,20]. Women were also largely dependent on their significant others for economic provisions, which, together with the existing gender and traditional norms, limited women’s ability and freedom to make family or health decisions to seek skilled care. Therefore, we developed an mHealth-based SS intervention (the Support-Moms intervention) using the health care use model by Andersen [61] that incorporates predisposing-, enabling-, and need-based factors to improve intervention uptake and service use. We then considered the framework by Bendixen et al [62] to personalize the information and tailor the system for our targeted end users. Our novel mHealth app was developed as part of a career development award (NIH-K43TW011004). This app or intervention was compatible with local regular mobile phone types, providing varying text and audio delivery mediums for individuals who were literate and who were not. In a randomized 3-arm pilot study (N=120) pregnant women who had not presented for ANC by their second trimester were equally randomized to receive (1) standard of care, which is the routine ANC information given at the maternity centers (control); (2) scheduled SMS audio messages from the final messaging prototype (scheduled messaging [SM]); and (3) SM, plus social supporter engagement through SMS (SS) [63].

We observed high intervention acceptability and feasibility, with >80% of women receiving ≥85% of intended messages within 1 hour. Over 95% of women found the app easy to use and compatible with their existing messaging programs; they also reported that the messages were useful and engaging and would strongly recommend the intervention to others. Nearly all women in the SS arm (39/40, 98%) had a skilled delivery compared to 78% (31/40) and 70% (28/40) of the women in the SM and control groups, respectively. All women whose social supporters were engaged on the app (SS arm: 40/40, 100%) attended ≥4 ANC visits, compared to 83% (33/40) and 50% (20/40) of the women in the SM and control groups, respectively. Fewer women (8/40, 20%) in the SS arm missed any visits due to the lack of transportation compared to 58% (23/40) and 68% (27/40) of the women in the SM and control groups, respectively. In addition, fewer maternal or fetal complications (3/40, 8%) were reported in the SS arm compared to 13% (5/40) and 25% (10/40) complications in the SM and control groups, respectively. Using the Duke-University of North Carolina (UNC) Functional Social Support scale [64], women in the SS arm reported improved SS (median 3.4, IQR 2.8-3.6) compared to 2.8 (IQR 2.6-3.2) and 2.4 (IQR 2.2-2.8) in the SM and control arms, respectively (score ranges from 1 to 4, and 4 indicates high levels of SS). In qualitative interviews, all women described the intervention as useful, actionable, and easy to use; tailored health information helped them to learn, internalize, and comprehend ANC and skilled delivery benefits, strengthening their informed decision-making as they were reportedly able to easily share and discuss information with their significant others, who in turn committed to providing them the needed support to prepare and seek help. Women also expressed that the involvement of their significant others within a friendly, trusted, and familiar environment helped them to mobilize needed support during pregnancy. Involving both health care providers (HCPs) and end users in characterizing, developing, and formulating the mHealth intervention allowed its tailoring to their preferences. Given the success in our pilot work where 78% (93/120) of the women used feature phones and promising preliminary efficacy data presented earlier [36,63], the next logical step was to assess the effectiveness, implementation, and scalability of such multiple messaging strategies to improve care access in SSA, where the contextual factors that drive successful interventions differ, but the public health impact of such interventions is likely to be the greatest [65].

### Objectives

We now propose a type 1 hybrid implementation-effectiveness trial to evaluate and implement this intervention into routine care. We will test the effectiveness of the intervention in a randomized controlled trial (aim 1). We will apply the implementation outcomes framework by Proctor et al [66] to evaluate implementation, service, and client outcomes and conduct in-depth interviews with users and key stakeholders to contextualize or clarify these outcomes as well as explore implementation strategies for future scale-up using the Consolidated Framework for Implementation Research (CFIR; aim 2). We will then assess the costs and cost-effectiveness of implementing the Support-Moms intervention into routine care (aim 3). We hypothesize that implementing Support-Moms will be an effective and cost-effective strategy to improve maternity service use.

## Methods

### Study Overview

We propose to evaluate the effectiveness and implementation of the Support-Moms app into routine care. We hypothesize that Support-Moms will improve maternity service use and reduce the MMR when integrated into routine care. We will test the effectiveness of the Support-Moms intervention in a randomized controlled design (aim 1); evaluate intervention implementation using the implementation outcomes framework by Proctor et al [66], as outlined in Figure 1 (aim 2); and then refine implementation strategies for future scale-up using the CFIR, as outlined in subsequent sections [67]. We will assess the cost and cost-effectiveness of implementing this intervention into routine care and its implication for sustainability (aim 3). These outcomes will serve as indicators of implementation success or necessary preconditions for attaining desired service outcomes for women in rural, resource-limited settings. This will enable us to identify practical, context-specific, and actionable strategies for achieving optimal implementation effectiveness at a low cost. The intervention strategies were developed in our pilot work together with facility HCPs. In the cost-effectiveness analysis, if Support-Moms and standard of care are found to have equivalent effectiveness, we will conduct a cost-minimization analysis where only the cost of Support-Moms per participant will be estimated and reported (no incremental cost-effectiveness ratios [ICERs] will be calculated). This alternative approach would remain informative to the policy makers and stakeholders in maternity service use. Notably, simultaneous assessment is warranted given the (1) strong preliminary evidence, (2) relatively low investment needed for costing, and (3) overall efficiency of our proposed type 1 hybrid effectiveness-implementation trial approach.

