### Aim 1: Testing the Effectiveness of the Novel Support-Moms Intervention in a Randomized Controlled Trial

We will enroll a cohort of 824 adult pregnant individuals with gestational ages ≤20 weeks at enrollment (determined by last normal menstrual period or ultrasound scan where available). Consenting participants will be randomized 1:1 at enrollment to standard of care (Ministry of Health [MOH] guidelines–based routine care and information giving, n=412, 50%) versus the Support-Moms (intervention) group (n=412, 50%). We will identify, screen, and enroll people through the existing CHWs or VHT structure from areas within a 10 km radius of all publicly funded maternity centers across Mbarara and Mitooma districts, who have not yet presented for ANC by the beginning of their second trimester. We will power the study to test the superiority of the Support-Moms intervention for our primary effectiveness outcome: HCP-led skilled birth delivery. Secondary outcomes will include (1) number of ANC visits, (2) institution-based delivery, (3) SS, (4) mode of infant delivery, (5) all deaths (maternal, fetal, and newborn), (6) preterm birth, (7) birth weight, (8) breastfeeding, (9) completion of postnatal care, and (10) complications of pregnancy and childbirth (eg, obstructed labor, ruptured uterus, need for neonatal or maternal resuscitation or assisted ventilation, severe preeclampsia or eclampsia, postpartum hemorrhage, maternal or newborn sepsis, and other infections).

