### Aim 1: Analysis Plan and Sample Size Calculations

We will first summarize health-related and sociodemographic data between arms. For our primary effectiveness outcome, HCP-led skilled birth delivery, we will fit a multivariable logistic regression model, with study arm as the predictor of interest, and age, high-risk pregnancy, and health facility at enrollment as a priori additional variables in the model, due to their strong association with the selected outcome [70,90,91]. In our primary intention-to-treat model, we will consider women with missing outcome data, after home visits and next of kin interviews, as presumed to have not received skilled birth (ie, there will be no missing outcome data in our primary analysis). In sensitivity analyses, we will (1) repeat the analysis after excluding women with missing outcome data and (2) include additional potential confounders in the model that may have persisted despite individual randomization (eg, number of previous deliveries at a facility, socioeconomic status, distance to facility, history of facility delivery, food insecurity, alcohol use, and depression). Although not designed to detect a difference, we will also explore additional secondary outcomes, including (1) number of ANC visits completed, (2) mode of infant delivery, (3) institution-based delivery, (4) presence of one or more birth complications, (5) child mortality, (6) maternal mortality, (7) preterm birth, (8) birth weight, (9) completion of postnatal care, (10) SS, and (11) initiation of breastfeeding. Both our pilot data and other similar studies estimate that 70% of the women in Uganda deliver with a skilled attendant [15,48,49]. Finally, we will explore the role of SS as a moderating effect of the intervention through a prespecified stratified analysis among women in the upper versus lower half of SS in the cohort, as measured by the Duke-UNC Functional Social Support Scale [64]. To test our primary effectiveness hypothesis, allowing for a 2-sided type I error of 5%, 90% power, and assuming a 5% loss to follow-up, we will require 824 participants to detect a 10% difference in HCP-led skilled birth delivery between arms. Data analysis will be conducted using Stata (version 17; StataCorp LLC). The findings will be presented as descriptive statistics, scatter plots, and graphs; statistical significance will be considered at *P*≤.05. While we will ensure completed data are collected through timely cleaning and REDCap prompts, we will still be able to detect the same effect in the primary outcome with the power of 85% in the unlikely event that we lost up to 18% of the records due to missing data.

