### Cost-Effectiveness Analysis

Cost analysis will include estimating program costs, costs to HCPs, and costs to users as described above. We will also develop a decision tree model to assess the potential impact of economic, clinical, or health outcomes of the Support-Moms intervention against routine care [101,102]. The model will incorporate cost items, relevant clinical probabilities, and case outcomes, allowing a cost-effectiveness evaluation. We will combine the costs and outcomes for each branch of the tree using branch possibilities to simulate the expected costs and outcomes of the intervention and routine care. We will hypothesize service users using routine maternity services or enrolled on the Support-Moms app (per trial arm) as they pass through different health states over time and within acute and chronic health states of 3 key maternal morbidities of sepsis, postpartum hemorrhage, and hypertensive disorders [70,103-105]. Our cost-effectiveness evaluation will account for the outcomes for both the mother and the infant throughout their lifetime at the annual discounting rate of 3% [106]. The clinical and cost outcomes for the infant (eg, low birth weight and stillbirth or intrauterine fetal deaths) will be incorporated in the decision tree. We will use 1-way and probabilistic sensitivity analyses to quantify the confidence level or robustness in this model analysis output in relation to the outputs and the payer’s willingness to pay thresholds [101,107]. We will estimate ICERs in terms of cost per additional HCP-led skilled birth delivery and per death averted. In addition, we will estimate ICERs per disability-adjusted life years averted and quality-adjusted life years (QALYs) gained (QALYs derived from the collected SF-6Dv2 data) as the main summary measures of cost-effectiveness [108] in line with the country’s gross domestic product per capita (GDPpc) [109], to assess the value for money of adopting or providing the Support-Moms app long-term compared to routine care. If ICERs per QALY or per disability-adjusted life years <300% of GDPpc, Support-Moms will be deemed cost-effective, highly cost-effective for ICERs <100% of GDPpc, and not cost-effective otherwise. The decision tree and cost-effectiveness analyses will be programmed in TreeAge (TreeAge Software, LLC).

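### An undefined finding of equivalence in a superiority-only trial cancels every ICER and leaves a one-arm cost, so a merely non-significant result could remove the cost-effectiveness comparison

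*Protocol article*

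**What the plan says.** The Study Overview sets a conditional rule for the economic analysis: "if Support-Moms and standard of care are found to have equivalent effectiveness, we will conduct a cost-minimization analysis". Under that condition "only the cost of Support-Moms per participant will be estimated and reported" and "no incremental cost-effectiveness ratios [ICERs] will be calculated". It does not say what counts as equivalent: no outcome, margin, test or confidence-interval rule is given.

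The only effectiveness test described is for superiority. The aim 1 section states: "We will power the study to test the superiority of the Support-Moms intervention for our primary effectiveness outcome". The sample size section gives its terms, "allowing for a 2-sided type I error of 5%, 90% power, and assuming a 5% loss to follow-up", and concludes that "we will require 824 participants to detect a 10% difference in HCP-led skilled birth delivery between arms". It also counts women with missing outcomes as not having had a skilled birth, so all 824 enter the primary analysis.

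The aim 3 section promises incremental cost and collects service-use costs from all aim 1 participants. The Cost-Effectiveness Analysis section plans ICERs per additional skilled birth, per death averted, per DALY and per QALY, with one-way and probabilistic sensitivity analyses. It attaches no equivalence condition and does not mention the switch. It ends with a GDP-per-capita rule: cost-effective below 300%, "highly cost-effective for ICERs <100% of GDPpc, and not cost-effective otherwise".

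**The concern.** A superiority test that fails to reject does not show that two arms are equivalent. With no margin stated and no other test described, non-significance is the likeliest working meaning of equivalent effectiveness. Whether the trial yields any cost-effectiveness estimate would then turn on the aim 1 P value, and a programme with a moderate real benefit could reach policy makers with a cost and no ICER.

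Three problems remain even if an analysis plan that is not shown defines the term.

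- **No comparison.** A cost-minimization analysis compares the costs of alternatives. The cost of one arm is not such a comparison, and reporting it alone sets aside control-arm costs that are already being collected.
- **Wrong outcome for the decision.** Similar skilled-birth rates would not make deaths, DALYs or QALYs similar. The article itself describes its secondary outcomes, which include the deaths, as ones the trial is not designed to separate.
- **Internal conflict.** One section cancels the ICERs under a condition that another section, which plans them in full, does not contain.

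**Working it through.** **Inputs.** Control rate 70%, target difference 10 points, two-sided 5%, 90% power, 5% loss, N = 824 (sample size section); 412 per arm (aim 1 section). All calculations are unadjusted normal approximations, whereas the planned model is an adjusted logistic regression.

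**1. The plan's own figure.** For 70% versus 80%, with pooled rate 0.75:

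n per arm = [1.960·√(2·0.75·0.25) + 1.282·√(0.70·0.30 + 0.80·0.20)]² / 0.10² = 391.9, so 392 per arm and 784 in total.

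For 5% loss, 784 × 1.05 = 823.2, rounded up to 824; 784 / 0.95 = 825.3, rounded up to 826. The stated 824 is reproduced. This is a superiority calculation only.

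**2. What a non-significant result can look like.** Take 412 per arm, because missing outcomes are counted as no skilled birth. For an observed 70% versus 75%:

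SE = √[(0.70·0.30 + 0.75·0.25)/412] = 0.0311

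95% CI = 5.0 ± 1.96·3.11 = 5.0 ± 6.1, or about -1.1 to +11.1 points.

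This is non-significant, yet it includes both zero and the 10-point design effect.

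**3. How often that happens.** Power = Φ[(d − 1.96·SE₀)/SE₁], where SE₀ uses the pooled rate and SE₁ the two separate rates:

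| True gain d | SE₀ | SE₁ | Power | No significant benefit |
|---|---|---|---|---|
| 5 points | 0.0311 | 0.0311 | 36.2% | 63.8% |
| 7 points | 0.0307 | 0.0307 | 62.5% | 37.5% |
| 8 points | 0.0306 | 0.0304 | 74.6% | 25.4% |
| 10 points | 0.0302 | 0.0300 | 91.4% | 8.6% |

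**4. Could the trial show equivalence properly?** The article gives no margin, so the margins here are assumptions. With two one-sided 5% tests, no true difference and 70% in both arms:

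SE = √(2·0.21/412) = 0.0319, and the 90% CI half-width is 1.645·3.19 = 5.3 points.

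Power = 2Φ(margin/SE − 1.645) − 1, set to 0 when negative:

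| Assumed margin | Power |
|---|---|
| 5 points | 0% |
| 6 points | 19% |
| 7 points | 42% |
| 8 points | 61% |
| 10 points | 86% |

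For 90% power, n per arm = 2·0.21·(1.645 + 1.645)²/margin², which is about 1,819 at 5 points and 455 at 10 points. The trial has reasonable power only at a margin near the difference it was built to detect.

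**5. The sections side by side.** Study Overview: under equivalence, one arm's cost and no ICERs. Aim 3 section: incremental cost, with service-use costs from participants in both arms. Cost-Effectiveness Analysis: four kinds of ICER, with probabilistic analysis against willingness-to-pay thresholds. The first cannot be carried out together with the other two as written.

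**The case against.** The strongest reply is that the article never ties the switch to a P value. A reader might infer that P above .05 is the stated trigger, but no section says so. A margin or confidence-interval rule could well sit in an analysis plan that is not shown. That is right, and it is why the point is that non-significance could trigger the switch, not that it would. It does not rescue the one-arm replacement, the conflict between sections, or the loss of ICERs on outcomes other than skilled birth.

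Other strong readings also fail:

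- **That aim 3 would be lost.** The intervention cost is still reported and costs are still collected from both arms. What goes is the incremental comparison.
- **That the switch acts when uncertainty is greatest.** Precision hardly depends on the result. At 412 per arm the 95% half-width is about 6.3 points at no difference, 6.0 at +6 and 5.9 at +10.
- **That an observed 6-point gain would be non-significant.** This is on the boundary. At 412 per arm the nearest whole counts, 288/412 and 313/412, differ by 6.07 points with a half-width of 6.05, so the interval just excludes zero. The 5-point case is the sound illustration.
- **That the GDP-per-capita rule would class a dearer, less effective programme as highly cost-effective.** Its ICER would be negative and so, read literally, below the cut-off. But the section speaks of QALYs gained and DALYs averted, which presupposes a health gain. This is a matter of wording to clarify.

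It is also fair to say that the primary outcome, the sample size and the primary analysis are untouched, and that the probabilistic analysis already planned covers most of what the remedy asks for.

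**Conclusion.** The concern holds in this limited form. The article fixes a rule that removes all ICERs on a finding that its superiority design has little capacity to establish and that it does not define. The substitute analysis lacks a comparator.

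If non-significance is taken as the trigger, true gains of 5, 7 and 8 points would lose their ICERs about 64%, 37.5% and 25% of the time. If a formal equivalence test is required, it has essentially no power at a 5-point margin and about 86% at 10 points when the arms are truly equal.

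These figures assume a 70% rate in control after missing outcomes are counted as failures, 412 per arm, and unadjusted comparisons. The first set also depends on the non-significance reading, which is an inference. The missing comparator cost, the conflict between the Study Overview and the aim 3 sections, and the dropping of ICERs per death, DALY and QALY depend on none of these assumptions.

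**What to change.** Delete the cost-minimization switch from the Study Overview. State instead that incremental cost and incremental effect will be estimated jointly from both arms whatever the aim 1 result. Uncertainty would come from the planned probabilistic sensitivity analysis, shown for example as incremental net monetary benefit with its interval or as a cost-effectiveness acceptability curve.

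As a secondary clarification in the Cost-Effectiveness Analysis section, apply the 100% and 300% GDP-per-capita cut-offs only where Support-Moms is both more costly and more effective, and report dominance in either direction separately.

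The cost is a few sentences. The cost data, the SF-6Dv2 data and the model are already planned, and neither the sample size nor the data collection changes. The wording should be settled before arm-level results are examined.
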